**Methods and analysis:**

This is a cluster randomised controlled trial to evaluate the clinical and cost-effectiveness of introducing a personalised guided consultation compared with usual UK NHS physiotherapy care. Physiotherapy services (n=16) will be randomised in a 1:1 ratio to either intervention (physiotherapy training package and personalised guided consultation incorporating a new prognostic tool) or control (usual care); 832 participants (416 in each arm) identified from participating physiotherapy service waiting lists aged 18 years or over with shoulder pain will be enrolled. Follow-up will occur at 3 time points: 6 weeks, 6 months and 12 months. The primary outcome will be the Shoulder Pain and Disability Index (SPADI) score over 12 months. Secondary outcomes include global perceived change of the shoulder condition, sleep, work absence and the impact of shoulder pain on work performance, healthcare utilisation and health-related quality of life (using EuroQol 5 Dimension 5 Level (EQ-5D-5L)). A multimethod process evaluation will investigate views and experiences of participants and physiotherapists, assess uptake, facilitators and barriers to delivery, and changes in factors assumed to explain intervention outcomes. Primary analysis of effectiveness will be by intention-to-treat, and a health economic evaluation will assess cost-utility of introducing the personalised consultation.

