### Randomisation

In line with a cluster RCT design, the NHS physiotherapy services will be the unit of randomisation. As the number of clusters will be small (envisaged to be up to eight clusters per arm), we will use block randomisation stratified by the size of the physiotherapy service, based on the average number of patients treated for shoulder pain (large sites≥150 per month, small sites<150 per month). We will use block sizes of 2 within each stratum to randomly allocate the physiotherapy services to the intervention or control arms. The randomisation sequence will be computer generated using *blockrand* in R.^21^

To minimise the risk of participation bias, all participants will receive the same PIS which informs participants that the study is looking at how the discussion between patients and physiotherapists can best be supported. The PIS does not refer to the trial having two arms (intervention and control). Participants will be asked to consent to participating in a study investigating the delivery of care for shoulder pain by physiotherapists, consisting of the completion of self-report questionnaires (over a period of 12 months). Participants will be informed that they can withdraw from the study at any time without giving a reason, and that a decision to withdraw will not affect their current or future healthcare.

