#### Sample size calculation

The sample size for the trial is based on previous studies using the SPADI^18 46^ and using data from the PANDA-S cohort study.^32^ The trial aims for 90% power to test the superiority of the intervention to usual care by physiotherapists for patients with shoulder pain. The calculations assume a 5% type I error (two-tailed) and aim to detect an effect size of 0.30 (8–10 point difference, SD 24–30) in the primary outcome.^47^ The calculation takes into account the clustering of individual participants by service (ICC 0.02)^48^ and likely loss to follow-up of 25% over the 12 month follow-up (inflationary effect on the sample size), repeated measurements^49^ and adjustment for baseline SPADI scores (deflationary effect). To achieve this, 416 participants per arm, or 832 in total, are required.

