#### Main trial analysis

Baseline characteristics of the physiotherapy service clusters, and individual participants will be described for each trial arm. This includes the primary outcome, secondary outcomes, process measures, predicted SPADI scores and the proportion of participants predicted to score 20 or lower on the SPADI, indicating recovery.

The primary intention-to-treat (ITT) analysis will use a hierarchical linear mixed regression model to compare offering the intervention with usual care on SPADI total scores over the 12 months follow-up. This model will account for repeated measures within individuals and clustering within physiotherapy services, using available data from all time points and assuming missing data are random. Analyses will adjust for baseline SPADI score, age, sex and physiotherapy cluster size. A non-responder analysis will assess the risk of attrition bias. Data for individuals who withdraw consent will be included up to the point of withdrawal.

We will report mean differences and standardised effect sizes (relative to the overall SD) for the primary outcome. The number (percentage) of participants in each trial arm scoring 20 or lower on the SPADI at 6 and 12 months follow-up will also be reported, which will be used to calculate the Number-Needed-to-Treat.

The model parameters will primarily be estimated using maximum likelihood estimation (MLE). To address potential issues due to the small number of clusters, restricted maximum likelihood estimation (RMLE) will also be used as a sensitivity analysis. This will include evaluations with and without the Kenward-Roger approximation correction^50^ for SE and df in estimating fixed effects.

Analysis of secondary outcomes will be carried out using an ITT approach, using a linear mixed model for numerical outcomes and generalised mixed logistic models for categorical outcomes. The models will be adjusted for baseline SPADI, age and sex (participant-level) and physiotherapy service cluster size. A sensitivity analysis will be considered if there is baseline imbalance between arms, with additional adjustment for baseline characteristics that are >10% different for categorical variables, or >2 times the SE for numerical variables. For work absence, performance and healthcare utilisation, the analysis will focus on 6 and 12 month follow-up data, as these measures are not collected at the 6 week follow-up.

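### The primary analysis of 16 clusters uses uncorrected maximum likelihood, with REML and Kenward-Roger only as sensitivity analyses, so the stated 5% type I error is not held (roughly 6–11% under assumed settings)

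*Protocol article*

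**What the plan says.** The Abstract (Methods and analysis) fixes the design: "Physiotherapy services (n=16) will be randomised in a 1:1 ratio". The Randomisation section acknowledges what this implies: "As the number of clusters will be small (envisaged to be up to eight clusters per arm").

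The Sample size calculation section sets the operating characteristics. "The calculations assume a 5% type I error (two-tailed"), and "The trial aims for 90% power to test the superiority of the intervention to usual care". The target is given as "aim to detect an effect size of 0.30 (8–10 point difference, SD 24–30) in the primary outcome", and the calculation "takes into account the clustering of individual participants by service (ICC 0.02"). It also allows for 25% loss and takes credit for repeated measurements and baseline adjustment. The result is 416 per arm.

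The Main trial analysis section specifies a hierarchical linear mixed model adjusted for baseline SPADI, age, sex and cluster size. On estimation it says: "The model parameters will primarily be estimated using maximum likelihood estimation (MLE"). It then raises the small number of clusters as a possible problem and answers it thus: "restricted maximum likelihood estimation (RMLE) will also be used as a sensitivity analysis", to be run both with and without Kenward-Roger. No standard error or df correction is attached to the primary fit, and its reference distribution (Wald z, likelihood ratio or t) is not stated.

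**The concern.** Services are randomised, so the arm effect is estimated between services. With an intercept, arm and service size as cluster-level terms, 16 services leave 16 − 3 = 13 df. Two things then go wrong with an uncorrected maximum likelihood fit:

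- The between-service variance is biased downwards, because no df are deducted for the cluster-level fixed effects.
- If the statistic is referred to a normal distribution, the critical value is 1.96 instead of the 2.16 that t on 13 df requires.

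Both errors make the primary confidence interval too narrow. The protocol sees the problem and names a remedy, but ranks the remedy below the uncorrected fit. If the two disagree, the plan as written makes the uncorrected result the headline for the trial's main effectiveness claim.

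**Working it through.** **Inputs from the protocol.** 16 services, 8 per arm; two-sided 5%; 90% power; effect 0.30 SD; ICC 0.02; 25% loss; 416 per arm. That is 416/8 = 52 enrolled per service, or 39 after loss. Cluster-level terms: intercept, arm, size (13 df).

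**Assumed, because not stated.** The reference distribution of the primary test, the coefficient of variation (CV) of cluster size, the effective ICC after averaging visits and adjusting for baseline, and the repeated-measures and baseline deflation.

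**Step 1: the plan's own figure.** Unclustered n per arm = 2(1.96 + 1.2816)²/0.30² = 233.5, so 234.

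- Design effect with 39 per service: 1 + 38 × 0.02 = 1.76, giving 234 × 1.76/0.75 = 549 per arm.
- Design effect with 52 per service: 1 + 51 × 0.02 = 2.02, giving 234 × 2.02/0.75 = 630 per arm.

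Reaching 416 needs a deflation factor of 416/549 = 0.76 or 416/630 = 0.66. The protocol does not give the correlations behind it, so 832 cannot be reproduced exactly. It is plausible: an assumed baseline correlation of 0.5 alone gives a factor of 1 − 0.5² = 0.75 and 549 × 0.75 = 412 per arm.

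**Step 2: large-ICC limit, equal clusters (closed form).** Maximum likelihood divides by 16 where 13 is correct, so its standard error is too small by √(13/16) = 0.901. The error of a Wald z test is then 2·P(t₁₃ > 1.96 × 0.901) = 10.1%.

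**Step 3: simulation under the null, equal clusters.** 16 × 39, participant-level means, 400,000 trials per row. Repeat runs agree to about 0.1 percentage point.

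| ICC | ML, z | ML, t₁₃ | REML, z | REML, t₁₃ |
|---|---|---|---|---|
| 0.01 | 7.3% | 4.9% | 5.8% | 3.8% |
| 0.02 | 8.8% | 6.2% | 6.6% | 4.5% |
| 0.03 | 9.5% | 6.8% | 7.0% | 4.8% |
| 0.05 | 9.9% | 7.2% | 7.1% | 4.9% |

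REML with t₁₃ stands in for Kenward-Roger. At ICC 0.02, about 4.3% of null trials are significant under ML with z but not under REML with t₁₃.

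**Step 4: simulation varying cluster size.** Mean 39 per cluster, 20,000 trials per row.

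| ICC | CV | ML, z | ML, likelihood ratio | ML, t₁₃ | REML, z | REML, t₁₃ |
|---|---|---|---|---|---|---|
| 0.02 | 0 | 8.6% | 7.3% | 6.1% | 6.5% | 4.3% |
| 0.02 | 0.4 | 9.3% | 7.7% | 6.6% | 6.8% | 4.7% |
| 0.02 | 0.65 | 10.3% | 8.3% | 7.4% | 7.6% | 5.4% |
| 0.03 | 0 | 9.2% | 7.7% | 6.7% | 6.8% | 4.6% |
| 0.03 | 0.4 | 9.9% | 8.1% | 7.2% | 7.2% | 4.8% |
| 0.03 | 0.65 | 10.9% | 8.6% | 8.1% | 7.8% | 5.6% |

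A smaller run (6,000 trials) at ICC 0.02 and CV 0.8 gave 11.1% for ML with z.

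**Step 5: power with a t reference.** Var = 2[0.02/8 + 0.98f/(8 × 39)], where f is the deflation applied to the within-service variance; the noncentrality is 0.30/√Var.

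| f (assumed) | Noncentrality | Power, z | Power, t₁₃ |
|---|---|---|---|
| 0.57 | 3.24 | 90% | 85% |
| 0.444 | 3.40 | 92.5% | 88.1% |
| 0.31 | 3.60 | 94.9% | 91.4% |

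The value 0.57 was solved for so that the normal formula returns 90%; it is not a protocol figure.

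**The case against.** The best defence is that nothing is absent. The protocol recognises the small number of clusters and prespecifies the corrected fit, so readers will see it beside the primary result. That is true, and the defect is therefore one of ordering. But no rule says which result prevails when they differ, so the primary label decides. Nor can this be left to an unseen analysis plan, which could reverse the order only by contradicting the protocol.

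A second objection stands in full. The protocol names an estimator, not a test, and says nothing on cluster-size variation. A reader might infer that the type I error is simply doubled. The documents do not support that as a fixed result. About 10% or more needs a Wald z test together with unequal clusters or a higher effective ICC. With equal clusters at ICC 0.02 the inflation is about 1.7 to 1.8 times, and the other tests compatible with the text give less. At ICC 0.01 with equal clusters, maximum likelihood with t₁₃ is at 4.9%, so the range depends on the ICC too.

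A reader might also infer that 90% power is missed. That is not established: neither the deflation nor the reference distribution used for the sample size is given, and one assumed setting keeps power above 90%.

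Finally, df rules for the secondary mixed logistic models are detail commonly left to an analysis plan, and no fault is found there.

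**Conclusion.** The choice is wrong as written. At the protocol's ICC of 0.02, every maximum likelihood test examined exceeds 5%:

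- Wald z: about 9% with equal clusters, and about 9–11% with unequal clusters or at an effective ICC of 0.03.
- Likelihood ratio: about 7–8% at ICC 0.02.
- Maximum likelihood with t₁₃: about 6–7% at ICC 0.02.

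Over ICC 0.02–0.03 the overall range is roughly 6–11%. REML with t₁₃ lies at about 4.3–5.6%. REML with a normal reference is still at about 6.5–8%, so changing the estimator without the df correction is not enough. These figures rest on 16 services, about 39 analysed per service, 13 df, the assumed cluster-size CVs, and t₁₃ as a proxy for Kenward-Roger. The direction is firm; the exact size is not. The effect on power is conditional: about 85% if 832 was set to give exactly 90% with a normal reference, and 88–91% under more favourable assumptions.

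**What to change.** Make REML with Kenward-Roger standard errors and df the primary analysis of SPADI, and move maximum likelihood to the sensitivity analyses. Recheck the 90% power with a t reference, and state the repeated-measures and baseline correlations used so that 832 can be reproduced.

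The cost is small. Both analyses are already planned, so this is a re-ordering in one or two sentences, with no new data and no change of design. The primary confidence interval becomes slightly wider, and the stated power may fall slightly. The change should be made before the analysis begins.

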#### Health economic analysis

A within-trial economic evaluation will assess the cost-effectiveness and cost-utility of the intervention versus usual care for shoulder pain over 12 months. Incremental analysis will estimate the cost per additional point improvement on the SPADI (cost-effectiveness) and per quality-adjusted life year (QALY) gained (cost-utility) from both NHS and societal perspectives. The EQ-5D-5L (collected at baseline, 6 weeks, 6 and 12 months) will be used to generate QALYs. Healthcare resource use information will capture costs related to delivery of the guided consultation and training package, usual care, medicines use and any additional primary and secondary healthcare required for shoulder pain. Information on time off work will capture productivity losses.

Mean costs and outcomes will be compared between trial arms, with missing data handled using multiple imputation. Statistical analysis will be done on an ITT basis, adjusting for clustering and baseline variables. Incremental cost-effectiveness ratios will be calculated, and uncertainty will be examined by estimating 95% CIs and cost-effectiveness acceptability curves (CEACs), which link the probability of the intervention being cost-effective to a range of potential threshold values that the health system may be willing to pay per additional QALY gained. Analysis will adopt methods reflecting the cluster randomised nature of the trial, by using a regression-based model of net benefits, with physiotherapy service as the cluster identifier. Dependent variables in the multilevel models will include costs, QALYs and net monetary benefits and model coefficient estimates of differences in these variables will be used as part of the incremental analysis.

A decision-analytical model will estimate long-term cost-utility of the intervention, using data from the trial, clinical expertise within the team, the PANDA-S cohort study^31^ and estimates from the literature on shoulder pain prognosis, costs and quality of life. Sensitivity analyses will explore parameter uncertainty, with probabilistic sensitivity analysis to generate CEACs. Value of information analysis will assess the value of additional data to reduce uncertainty.

#### Process evaluation analysis

Semistructured interviews will be video or audio-recorded, transcribed, anonymised and analysed using two stages. First, an inductive thematic analysis^51^ will identify themes, followed by mapping these themes onto two theoretical frameworks:

*Normalisation Process Theory* (NPT),^52^ which explores how interventions are adopted and integrated into clinical practice through four components: coherence, cognitive participation, collective action, and reflexive monitoring.*COM-B model,*^53^ which examines behaviour change of both those delivering (physiotherapists) and receiving the intervention (people with shoulder pain) through capability, opportunity and motivation, extending the Theoretical Domains Framework.^54^

A coding framework will be developed from early transcripts and then applied to the remaining interviews and refined iteratively. Researchers will compare the views of participants and physiotherapists, analysing data for consistency and variation and aligning themes with NPT and COM-B components.

Audio-recorded consultations will undergo in-depth analysis using theme-oriented discourse analysis.^55^ This method will focus on the linguistic features and interactional strategies used by patients and clinicians during consultations. Researchers will transcribe and analyse content, paralinguistic features, such as pauses and intonation, and discursive strategies employed by people with shoulder pain and physiotherapists, to understand how the intervention is used and how participants engage with it. The team will discuss and agree on interpretations across consultations.

Data from CRFs and consultation summaries will be analysed using descriptive methods and will provide information on the physiotherapists’ opinions on the shoulder pain presented by patients. The analysis will assess the extent to which the three components of the guided consultation have been taken up, the time spent and the type of treatments and self-management resources offered. Physiotherapist comments on barriers and/or facilitators during consultations will be reviewed and categorised according to themes from the interviews and recordings.

#### Mediation analysis

Data from patient questionnaires will be analysed as potential mediators of the guided consultation’s effect. Mediation models for longitudinal data, using structural equation modelling or the outcomes framework, will estimate how changes in mediators explain the intervention’s impact on the primary outcome through indirect pathways.

### Trial monitoring

The PSC was appointed and approved by the funders to oversee the scientific conduct of the programme grant. Providing independent oversight of the trial, the PSC includes a chair, patient partner, senior statistical representative and two experienced clinical academics with relevant expertise. The committee met during the set-up of the trial and will meet every 6 months thereafter, for the duration of the trial. Given the low risk of the trial, the PSC and funders agreed that an independent Data Monitoring Committee (DMC) was not needed. Data monitoring responsibilities have therefore been adopted by the PSC.

Reporting to the PSC, a Trial Management Group (TMG) has been formed and comprises the chief investigator, associate investigators, coapplicants, trial managers from Keele University CTU and statistician plus other stakeholders as required. In addition to the management and monitoring of the trial, the TMG is responsible for optimal delivery of the trial, analysis and interpretation of the results.

### Safety reporting

In the PANDA-S trial, the guided consultation involves introduction of preconsultation form, a semistructured assessment, consultation summary documents and personalised information and advice. Adverse events (AEs) are expected to be rare and minor. Events such as temporary pain or discomfort from physiotherapy assessments and hospital treatments for planned shoulder surgeries will not be recorded as highly unlikely to be related to the intervention. However, if a participant becomes distressed during the delivery of the guided consultation and the physiotherapist deems this related to the intervention, it will be reported as AE. In the event of either an AE or serious adverse events (SAEs), there are systems in place to inform the CTU. Any SAEs will be reported to the Research Ethics Committee (REC) within the relevant time frame, and to the Trial Steering Committee as appropriate.

## Ethical considerations

### Ethics approval

This trial was provided with ethical approval by the Yorkshire & The Humber (South Yorkshire) Research Ethics Committee (REC reference: 23/YH/0070) on 28 April 2023.

### Participant consent

A Model Agreement for Non-Commercial Research^56^ will be signed by the sponsor at Keele University prior to randomisation outlining the responsibilities of all participating physiotherapy services. Written informed consent for data collection will be obtained from eligible participants presenting with shoulder pain who are willing to participate in the trial (see online supplemental material).

### Regulatory compliance

The PANDA-S trial will follow Good Clinical Practice (GCP) principles and the UK Policy Framework for Health and Social Care Research (HSCR). Keele University, as the sponsor, has a HSCR Quality Management System with Standard Operating Procedures in place which will be adhered to in the conduct of the trial. An independent external audit may be carried out by the sponsor. For quality assurance purposes, trials supported by the sponsor may be subject to an independent audit. The Head of Project Assurance at Keele University (the trial sponsor) can be contacted by email: [contact].

### Modification of the protocol

The trial sponsor will be notified of all amendments to the protocol.

### Protocol compliance

Deviations from the protocol and GCP will be documented. Keele CTU will implement corrective and preventative actions where appropriate. The Chief Investigator will take responsibility for these actions, with approval from the PSC if necessary.

### Data protection and patient confidentiality

All information collected during the trial will be kept strictly confidential and securely managed by Keele University through the CTU. Keele CTU adheres to General Data Protection Regulation^57^ and maintains a duty of confidentiality. All sensitive and personal electronic data will be stored in the CTU’s secure virtual network, requiring two-factor authentication for access. User roles and permissions will limit access to specific data and operations. After data collection has been completed, all data will be anonymised and cannot be linked to identifiable participants. Hard copies, such as consent forms, will be securely stored in lockable filing cabinets at Keele CTU.

### Post-trial care

All participants will receive care from their treating physiotherapist. The trial will not provide treatment or make recommendations regarding specific diagnostic procedures or clinical treatments, either during or after its completion.

### Access to the final trial data set

Keele University, a member of the UK Reproducibility Network, is committed to the principles of the UK Concordat on Open Research Data. Keele CTU has a longstanding commitment to sharing trial data to enhance research reproducibility and maximise benefits for patients, the public and the health and social care system. All data are available on following the School of Medicine at Keele University data request process by contacting the corresponding author and [contact].

